### Data handling and safety

All data is stored pseudonymized. Data of individual participants cannot be traced back. Personal data of the patients will be saved separately for further contacts of the families. The procedures to save and store the data adhere to German data protection laws.

### Data safety monitoring board

An independent data safety monitoring board consisting of an obstetrician and neonatologist, both with broad clinical expertise and experience in scientific trials will assemble on regular basis to review data quality, study procedures, CRFs, safety and results.

### Quality insurance and safety

If any unwanted events appear during the intake of probiotic or postpartum the women are obliged to contact us immediately. The study will be conducted, data recorded according to the protocol, the standard operating procedures (SOP) of our both clinics, the Good Clinical Practice (GCP) and the connected regulations and requirements.

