### Intervention/Control

Study participants are randomly assigned to receive the probiotic mixture (intervention group *n* = 73) or not (control group *n* = 73). The intervention is one capsule of Bactiol^®^ Infantis per day until delivery. The proposed number of participants is calculated based on former studies (see below). A randomization sequence was created in advance to assign mother – infant pairs to a study arm. This trial is not blinded. The women and participating doctors know whether they are in the intervention or control group, and we are not using a placebo.

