### Primary endpoint, secondary endpoints/data collection

The primary endpoint is the HMO composition (3-fucosyllactose, 3’-sialyllactose) in human breast milk after supplementation prenatally. Secondary endpoints are clinical and safety outcomes of mothers (infections, alterations in vaginal microbiome) and infants (preterm birth, sepsis, growth, gastrointestinal complications) and the effects on the microbiome composition in the rectovaginal tract of mothers at delivery and in the gut of term and preterm infants.

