### Data collection

Standardized Case Report Forms (CRFs) are used to record information from the mother prenatally and postnatally from mother and infant. At the time of inclusion (CRF inclusion), closely after birth (CRF day 3), one month after birth (CRF day 28), at three months CRF 3 m (mother + infant), one- and five-year follow- up (CRF 12 and 60 m) (see Fig. 2).

Data collected at the follow-ups will be used to measure long-term outcomes (allergies, incidence of infections, re-admissions to the hospital). The CRFs are filled in manually by the study team (neonatologist, doctoral student and study nurse). Additionally, the women will be asked to keep a diary handed out at inclusion to document regularity of probiotic intake, infections, antibiotic therapy, allergies and possible side effects during the intake of probiotics. The inclusion-CRF collects information of former participant’s medical history e.g. preexistent diseases, the course of pregnancy, former pregnancies and allergies. The follow up CRFs collect data from both, mothers and infants. CRF day 3 includes information about the delivery mode, reason for delivery, infections and risk factors for microbiome dysbiosis. In CRF day 28 information about complications in puerperium, growth parameters and feeding of the infant is collected. This data will be collected via telephone interview. In case of birth before completed 32 weeks follow-up examination will take place onsite. At follow-up information on both, mother and infant will be recorded via CRFs.

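### The antenatal duty to report unwanted events and the diary's side-effect item are tied to probiotic intake, which risks unequal ascertainment between arms

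*Protocol article*

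**What the plan says.** All references are to the protocol article.

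- **Duty to report** (Quality insurance and safety): "If any unwanted events appear during the intake of probiotic or postpartum the women are obliged to contact us immediately".
- **Diary** (Data collection): "the women will be asked to keep a diary handed out at inclusion to document regularity of probiotic intake, infections, antibiotic therapy, allergies". The list ends with "allergies and possible side effects during the intake of probiotics".
- **Arms** (Intervention/Control): "The intervention is one capsule of Bactiol^®^ Infantis per day until delivery". On the control condition: "The women and participating doctors know whether they are in the intervention or control group, and we are not using a placebo".
- **Endpoints** (Primary endpoint, secondary endpoints/data collection): "Secondary endpoints are clinical and safety outcomes of mothers", with infections and the vaginal microbiome named as the maternal items.
- **Other collection** (Data collection; Sample collection): case report forms cover the mother before and after birth, with no limit to one arm. The forms listed are one at inclusion, one at day 3 after birth and later ones. The day-3 form includes infections and the reason for delivery. A first-week questionnaire covers infections and allergies.
- **Oversight** (Data safety monitoring board): the board reviews safety, among other things.

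**The concern.** In a randomised comparison, the period over which events are counted should start at randomisation and run alike in both arms. Here the antenatal part of the reporting duty is defined by exposure. A woman on capsules is told to call from her first capsule. A control woman, who has no intake period, is on a literal reading told to call only after birth. The diary item for side effects repeats the tie.

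The wording also has a gap inside the probiotic arm. The Stopping rules foresee interrupted intake. Events between the last capsule and delivery fall outside the literal window, possibly including events that led to stopping.

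Controls are the only yardstick for background events in women with conditions such as PPROM, bleeding or preeclampsia. If their unwanted events are solicited less, the probiotic could look worse than it is. The gap after stopping pulls the other way, so the net direction is not predictable. The monitoring board would be reading the same unevenly collected data.

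**Working it through.** The point rests on wording, and no figure in the article depends on it. The check therefore sets out which antenatal information has a route to the record in each arm.

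**Step 1. Routes that do not depend on arm.**
- Infections: diary, first-week questionnaire and day-3 form.
- Antibiotic therapy: diary.
- Allergies: diary and questionnaire.
- Vaginal microbiome: swabs at inclusion and at delivery.
- Preterm birth, sepsis, growth and gastrointestinal complications: outcomes of the study as a whole, not dependent on a woman calling in.

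**Step 2. Routes tied to intake.** These are the duty to report unwanted events and the diary's side-effect item. For an unwanted event outside the list in Step 1, they are the only antenatal routes the article names. No form is listed between inclusion and day 3 after birth, and the stated content of the day-3 form has no general unwanted-event item.

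**Step 3. How far the diary phrase reaches.** The closing words on intake can qualify only the side effects, or the whole list. The narrower reading is the more natural one, and under it infections, antibiotics and allergies are collected in both arms. The wider reading is possible but not compelled. Under both readings, general unwanted events have no clear antenatal item for controls.

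**Step 4. Illustration of size.** The only input from the article is 73 women per arm (Intervention/Control). Everything else is assumed: the same true antenatal risk p in both arms, full capture on probiotic, and a captured fraction c in controls.

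- Apparent difference: p − p·c = p(1 − c).
- Chance of a nominally significant false excess on probiotic, two-sided 5% level: Φ[(d − 1.96·se0)/se1]. Here d = p(1 − c), se0 is the pooled and se1 the unpooled standard error.
- Example, p = 0.20 and c = 0.5: d = 0.20 − 0.10 = 0.10; se0 = √(0.15 × 0.85 × 2/73) = 0.0591; se1 = √((0.20 × 0.80 + 0.10 × 0.90)/73) = 0.0585. This gives Φ[(0.10 − 0.1158)/0.0585] = Φ(−0.27) ≈ 0.39.

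| True risk p | Control capture c | Spurious difference | Chance of false excess |
|---|---|---|---|
| 10% | 75% | 2.5 points | about 8% |
| 10% | 50% | 5 points | about 21% |
| 10% | 0% | 10 points | about 80% |
| 20% | 75% | 5 points | about 12% |
| 20% | 50% | 10 points | about 39% |
| 20% | 0% | 20 points | about 99% |

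With equal capture the difference is 0 and the two-sided error rate stays at 5%. The 0% rows apply only to events that no diary, questionnaire or case report form item collects. They do not describe infections.

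**The case against.** The strongest reply is that the sentence on unwanted events tells participants when to call and is not a rule for ascertaining endpoints. The same section refers conduct and recording to the protocol, operating procedures and GCP, and a journal article need not reproduce adverse-event forms. The diary goes to the women at inclusion, and the study team fills in the case report forms. The Statistical analysis section plans subgroups by antibiotic exposure and by infections in pregnancy, which presupposes those data in both arms. No between-arm test of unwanted-event rates is stated. Readiness to report in an open-label trial follows from the declared design ("This trial is not blinded"), and new wording would not remove it.

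Most of this stands, and it limits the point. A reader might infer that control women have no antenatal reporting at all, that the safety comparison is therefore biased, or that a real effect on maternal infections could be hidden. The document does not support these readings, because infections, antibiotic use and allergies have routes not restricted by arm.

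The reply does not remove the point. The article does not leave the window to another document: it states one, and defines it by exposure. An instruction on when to call also determines which events become known. Open-label reporting differences cannot be removed, but that is no reason to add a difference in the stated window.

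**Conclusion.** The point holds in limited form. As written, the antenatal duty to report and the side-effect diary item leave out control women, and also probiotic women between their last capsule and delivery. This is a risk of differential ascertainment, not a demonstrated bias. It falls mainly on unwanted events outside the infections, antibiotic use, allergies and obstetric or infant outcomes that are collected without restriction by arm.

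Its size cannot be fixed, since the article gives neither event risks nor capture fractions. The percentages above depend wholly on the assumed values, and they test an event rate for which the article states no formal comparison. The conclusion rests on reading the two sentences literally. If the operating procedures already apply the same window to all women, correcting the wording is enough. The change is worth making because maternal safety outcomes are secondary endpoints and it costs almost nothing.

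**What to change.** 1. Define the reporting window in both arms as randomisation to delivery, followed by the postpartum period, whether or not capsules are still being taken.
2. Use one diary with identical items on infections, antibiotics, allergies and unwanted events. Keep only the item on capsule regularity specific to the probiotic arm.
3. Compare arms only on items collected identically. Report side effects attributed to intake descriptively for the probiotic arm.
4. Flag data collected under the present wording whenever arms are compared on unwanted events.

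The cost is a change of wording in the protocol and diary, with no extra visits or staff. The drawback is that data gathered before and after the change will not be fully comparable, which is why step 4 is needed.

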### Data sharing and dissemination

Authorship of resulting manuscripts will be based on guidelines of the International Committee of Medical Journal Editors. Involved parties will be informed in cases of important modifications. The results of this study will be published in peer-review journals and presented at scientific meetings, which will enable discussions with scientific community.

## Conclusion

This is a prospective randomized intervention study supplementing probiotics to women with imminent preterm birth. We propose to support HMO composition in breast milk and consequently to increase the abundance of favorable bacterial groups (primarily *Bifidobacteria* spp.) in the neonatal microbiome. The aim of this study is to improve clinical neonatal outcomes by optimizing the supply of HMOs in human breast milk in order to create improved conditions for the establishment of a healthy neonatal microbiome. Further, we aim at defining microbiome signatures of the women’s vaginal flora that are associated with probiotic intake and HMO composition. We hope to learn more about the complex coevolution of pregnant women’s gut microbiome, immune modulating components of human breast milk (e.g. lactoferrin, IgA or glycomacropeptide) and immune function of the newborn [57, 58]. The biophysiological mechanisms of this coevolution is described by the concept of an “*entero – mammary – (neonatal) gut pathway*” which not only seems to determine the supply of commensal bacteria in breast milk at the critical timeframe of neonatal microbiome establishment within the first weeks of life. Immune factors, cytokines, regulatory cells and antibodies are translocated in a similar manner to potentially affect and shape neonatal vulnerability in the “*window of opportunity*” after delivery. That the *entero – mammary – gut pathway* can be successfully targeted by probiotic supplementation of pregnant women has been previously demonstrated by a randomized placebo-controlled trial (RCT) that measured elevated concentrations of *Bifidobacteria* spp. in breast milk of treated women when compared to untreated controls [35]. Notably, various (patho)physiological elements in this context have not yet been studied in detail, including determinants of HMO synthetization in the mammary glands. However, previous studies point towards more complex translocation processes that are stimulated by probiotic supplementation during pregnancy. These processes in passive immunization and antibody translocation as well as HMO supply in expressed breast milk.

Probiotics are widely used in preterm infants as a NEC prophylaxis [51, 52] and were supplemented to pregnant women within clinical trials [1]. To identify the scientific value of this study, we performed a literature review on probiotic supplementation during pregnancy reporting on various maternal and neonatal outcome parameters. Interestingly, RCTs using *Lactobacillus acidophilus* and *Bifidobacterium animals subsp. lactis and B. infantis* probiotics not only showed a significant impact on maternal outcomes such as decreased rates of GDM [31] or reduced colonization rates with group B Streptococcus [37], but as well demonstrated significant measurable effects on neonatal characteristics such as microbiome composition, immune phenotype (cytokine secretion) and rates of atopic symptoms [40, 41]. In conclusion, however, study results are largely inconclusive across the studies performed, which might mainly be due to differences of in- and exclusion criteria, dosage of probiotic supplements and most importantly, targeted outcomes. To our best knowledge and as a result of our literature review, only one study has investigated HMO composition of human breast milk after probiotic supplementation of pregnant women. While demonstrating promising results by showing increased levels of several breast milk HMOs after birth, the study was limited to included pregnancies of > 36 weeks and infants born at term. Hence, the effects of probiotic supplementation have so far never been studied in the context of HMO breast milk composition at preterm birth. Our main hypothesis is that supplementation of *Lactobacillus acidophilus* and *Bifidobacterium animals subsp. lactis and Bifidobacterium infantis* during pregnancy will increase the abundance of HMOs at the time of preterm delivery. Based on the findings of Seppo et al. [1], we propose changes of the concentration of 3’-fucosyllactose and 3’-sialyllactose in women supplemented with probiotics when compared to non-treated controls. Our second hypothesis of vaginal microbiome signatures that are associated with probiotic intake are based on study results showing a reduction in vaginal dysbiosis and increased amounts of favorable bacteria [35, 39, 59]. As a secondary outcome we will explore signatures of the neonatal microbiome of supplemented mothers as compared with non-supplemented controls. Previous observational studies and RCTs indicate that probiotics are safe and well tolerated in an adequate clinical setting. Results of this study may have implications for the management of pregnancies at risk for preterm delivery. A stable neonatal microbiome and dysbiosis prevention may improve short and long-term outcomes of preterm infants. If this study confirms our hypotheses, placebo-controlled randomized trials will be necessary to verify the results.

## Data Availability

No datasets were generated or analysed during the current study.

## Abbreviations

C: Candida
CFU: Colony forming unit
CRF: Case report form
DNA: Desoxyribonucleic acid
FGF-ß: Fibroblast growth factor beta
GABA: Gamma-aminobutyric acid
GAD: Gamma decarboxylase
GBS: Group B streptococcus
GCP: Good clinical practise
GDM: Gestational diabetes mellitus
GLU: Glutamate
GWG: Gestational weight gain
HbA_1_C: Glycolyzed hemoglobin
HMO: Human milk oligosaccharide
IL: Interleukin
L: Lactobacillus
MDA: Malondialdehyde
NEC: Necrotizing enterocolitis
RCT: Randomized controlled trial
rRNA: Ribosomal ribonucleic acid
SCFA: Short chain fatty acids
SOP: Standard operating procedures
SPT: Skin prick test
T_H_-1: T-helper lymphocyte
Treg T: regulatory lymphocyte
